### Statistical analysis

We will conduct analyses involving three-level multilevel models, with women’s weekly purchasing data clustered within women, who are clustered within stores. Weekly purchasing data are not normally distributed and therefore an alternative continuous distribution such as the negative binomial distribution will be considered or a binary variable will be used. With the data in ‘long’ format, an interaction between intervention group and time period will indicate whether there is a difference in change in sales from the 3-month baseline period to the 0–3 months and 3–6 months periods postintervention between the control and intervention stores. These models will be adjusted for sales from the 3-month baseline period as an efficient analysis of the changes in purchasing taking account of regression to the mean.^38^

Effect modification by educational level will be assessed by including a multiplicative interaction between intervention group and education level in the individual purchasing models. If there is evidence of an interaction, stratified analyses will be performed to determine the strength and direction of intervention effects for each level of educational attainment.

Women’s dietary quality scores (SD) will be calculated at baseline, 3 and 6 months. Multilevel linear regression models (with women clustered within stores) will be used with dietary quality score as the outcome measure, intervention group as the exposure and baseline diet scores included in the model to account for regression to the mean.^38^ Confounders will be determined by a directed acyclic graph.^39^ Analyses of other secondary outcomes (ie, daily fruit and vegetable intake and child’s dietary quality) will adopt the same statistical approach as that for women’s dietary quality.

Store sales data will be analysed using multilevel models to account for the clustering of weeks within stores. Weekly sales data will be the outcome and will be transformed to normality using Fisher-Yates transformations.^40^ Analyses will use interrupted time series models^41^ with CIs calculated at the 3 and 6 months postintervention commencement time points using the delta method.^42^ Statistical analyses will be conducted in Stata.^43^

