### Study setting

WRAPPED focuses on women from disadvantaged backgrounds and will, therefore, sample from customer who shop at stores of the collaborating discount supermarket chain situated in more socioeconomically deprived neighbourhoods across England. The collaborating supermarket has over 900 stores nationwide and holds approximately 2% of the grocery market share in the UK.^23^

This study will sample 36 stores, 18 intervention and 18 control stores; allocation to intervention condition will be at the store level. Intervention stores will be selected, in a phased approach, from the collaborating supermarket’s ongoing refurbishment programme. Randomised controlled trial methodology in real-world supermarket research is limited because it requires commitment that is problematic in this highly competitive, commercial setting. In WRAPPED, randomisation of stores is also not viable within the company’s business model. Consequently, control stores will be matched to an intervention store based on: (1) sales profile, (2) customer profile and (3) neighbourhood deprivation (Index of Multiple Deprivation).^24^Matching on these factors increases the similarity of intervention and control stores and reduces effects of confounding. We will seek to select control stores located at least 20 miles from an intervention store to reduce contamination effects of control women shopping at intervention stores.

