#### Primary outcome

The primary outcome is change in participant’s weekly fruit and vegetable purchasing patterns from baseline (3 months prior to refurbishment) to the 3–6 months period postrefurbishment. Change in fruit and vegetable purchasing from baseline to the 0–3 months period postrefurbishment will also be assessed to measure short-term purchasing effects. These data will be obtained through the supermarket chain’s loyalty card scheme and provide information about the number of items for each product purchased at each store visit during the study period. We will also examine sales of frozen fruit and vegetables (for substitution effects). The research team will aggregate these data from each visit to a weekly structure for analysis to enable our data to be presented as items (bags of fruit/vegetables because these products are not sold singly at the collaborating supermarket chain) per household per week which is comparable to analyses conducted in previous supermarket trials.^27 29^

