
### Sample size calculations

The study will be powered to detect differences in the primary outcome (fresh fruit and vegetable purchasing) between women in the intervention and control groups during the 3–6 months postintervention period. We used data from our previous research on women in Hampshire who were the same age range as the proposed participants of this study^15^ and considered the supermarkets at which the women shopped as clusters to estimate an r of 0.1 as our intraclass correlation coefficient. We aim to detect a difference of 0.3 item/average bag of fruit/vegetables (1.5 portions) per week. Assuming an SD of 0.7 item (3.5 portions) per week as seen in the pilot data, 16 stores in each arm and 30 women per store provides 90% power at a 5% significance level (two sided).

The study will also be powered to assess the secondary outcome of women’s dietary quality. Our previous research provided a rho of 0.1 as our intraclass correlation coefficient and a correlation coefficient of 0.8 for the means of women’s dietary quality at the store level between baseline and 2-year follow-up. Taking account of the clustering, and using the method of Teerenstra *et al*
36 to adjust for the method of analysis planned (adjusting diet quality score for baseline in the analyses), 16 stores in each arm with 30 women per store provides 85% power at a 5% significance level (two sided) to detect a difference in the diet quality scores at follow-up of 0.23 SD. Additionally, assuming that half the women have children aged 2–6 years, 16 stores in each arm will also provide 80% power to detect a difference in the children’s diet quality scores of 0.25 SD using the methods described above. Having fewer participants but retaining the full number of clusters has relatively little impact on the anticipated power.^37^ The recruitment plan will oversample with 18 stores in each arm to account for potential store closure and up to 45 women per store to account for attrition.

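### If the primary three-level model carries random intercepts only, its group-by-period test omits between-store variation in change and is anti-conservative

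*Protocol article*

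**What the plan says.** All references are to the protocol article.

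- Study setting: "allocation to intervention condition will be at the store level". Stores are matched, not randomised.
- Primary outcome: "change in participant’s weekly fruit and vegetable purchasing patterns from baseline (3 months prior to refurbishment) to the 3–6 months period postrefurbishment".
- Statistical analysis, structure: "three-level multilevel models, with women’s weekly purchasing data clustered within women, who are clustered within stores".
- Statistical analysis, test: "an interaction between intervention group and time period will indicate whether there is a difference in change in sales from the 3-month baseline period". This contrast is made for both post-refurbishment periods, on long-format records.
- Statistical analysis, next sentence: "These models will be adjusted for sales from the 3-month baseline period as an efficient analysis of the changes in purchasing".
- Statistical analysis, distribution: "an alternative continuous distribution such as the negative binomial distribution will be considered or a binary variable will be used".
- Sample size calculations: a difference of 0.3 item per week between groups during months 3–6, SD 0.7, intraclass correlation 0.1, and 16 stores per arm with 30 women each, for 90% power at a two-sided 5% level. A store-level correlation over time of 0.8 is given, but only for mean diet quality between baseline and 2 years.

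The article neither mentions a random period effect at store or woman level nor rules one out.

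**The concern.** The layout change is applied to stores. The uncertainty of its effect must therefore include how differently stores would have changed anyway, for instance through local competition. Replication for that source of variation is 16 stores per arm.

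A store intercept and a woman intercept are the same in every period, so both vanish when one period is subtracted from another. A woman's baseline purchasing is also constant across her rows, so in a balanced Gaussian model the covariate vanishes from the contrast too. What remains in the model's standard error is week-to-week noise averaged over 16 × 30 × 13 = 6,240 woman-weeks per arm and period, taking 3 months as 13 weeks. The sample size counts stores, but this analysis would effectively count weeks.

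At stake are the nominal 5% level and the interval width for the primary outcome of a study meant to inform policy.

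**Working it through.** **1. Reproduce the planned power.** Design effect = 1 + (30 − 1) × 0.1 = 3.9. Effective number per arm = 480 / 3.9 = 123.1. SE = 0.7 × √(2 / 123.1) = 0.089. Power for 0.3 is 92.0% (normal) or 90.2% (t, 30 degrees of freedom). The stated 90% reproduces, with the full store correlation in the SE.

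**2. Which weeks are in the outcome?** If only post-refurbishment weeks were modelled, a group-by-period interaction would compare the 0–3 month effect with the 3–6 month effect. It could not show change from baseline. The interaction sentence therefore needs baseline weeks in the outcome.

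**3. Inputs for the contrast.** From the document: SD 0.7 and correlation 0.1, giving store variance 0.1 × 0.49 = 0.049 and woman variance 0.441. Here 0.7 is taken as the between-woman SD of period means. Assumed, because the document gives no figure: weekly residual variance s² of 0.49 to 2.0; store between-period correlation r of 0.80 to 1; woman between-period correlation of 0.8 or 1; normal outcomes.

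**4. Formulas for the difference in change between arms.**
- Random-intercept SE = √(4 × s² / 6,240)
- True SE = √(4 × [0.049(1 − r)/16 + woman-by-period variance/480 + s²/6,240])
- Type I error = 2 × [1 − Φ(1.96 / ratio)], where ratio = true SE / model SE

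**5. Worked example**, s² = 1.0, woman correlation 1.
- Model SE = √(4 / 6,240) = 0.025.
- r = 0.95: store-by-period variance 0.00245; true SE = √(4 × [0.000153 + 0.000160]) = 0.035; ratio 1.40; type I error about 16%.
- r = 0.80: store-by-period variance 0.0098; true SE = √(4 × [0.000613 + 0.000160]) = 0.056; ratio 2.19; type I error about 37%.

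**6. Range over s² from 2.0 down to 0.49.**

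| Store r | Woman correlation | Type I error |
|---|---|---|
| 1 | 1 | 5% |
| 1 | 0.8 | 11–26% |
| 0.95 | 1 | 11–25% |
| 0.90 | 1 | 16–38% |
| 0.80 | 1 | 25–51% |
| 0.80 | 0.8 | 29–54% |

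The model SE is about 0.018–0.036, against 0.089 in step 1. The true SE at r = 0.80 is 0.053–0.067.

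**7. Simulation**, 1,000 null trials per setting. At s² = 1.0 and woman correlation 1, the random-intercept test rejected in 16%, 24% and 37% of trials at r = 0.95, 0.90 and 0.80. A store-level t-test on change rejected in 4–7% across all settings. With post-refurbishment weeks only, baseline as covariate and a store intercept, rejection was 5–7% for months 3–6 alone and 5–12% with both post periods in one model.

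**The case against.** A reader might infer that the planned model has no store-by-period term and that the primary test is therefore strongly anti-conservative. The document does not support that as a fact.

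- The missing term is inferred from silence. Naming three levels describes the hierarchy, not the whole covariance structure, and a condensed article may leave random slopes to an analysis plan that is not shown. This stands, and it makes the point conditional.
- The baseline-adjustment sentence may mean a model of post-refurbishment weeks with baseline as covariate, and the sample size section also frames the comparison within months 3–6. On that reading inflation is nil to mild (5–12%). This stands as a possible intention, but it does not fit the sentence defining the interaction. The two sentences need reconciling.
- The size rests on unstated quantities. The 0.8 concerns observed store means of diet quality over 2 years, not store effects on purchasing over months. Residual variance is assumed, and neither the negative binomial nor the binary model was simulated. This stands for the size; the direction does not depend on 0.8, since inflation already appears at 0.95.
- Matched stores recruit in the same period, so seasonal shifts shared within a pair largely cancel between arms. This also stands; only store-specific change matters.
- The 90% power figure is sound, and nothing here disputes it.

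**Conclusion.** The point holds conditionally. The section gives baseline two roles and does not make clear that between-store variation in change enters the standard error of the primary contrast. If the three levels are random intercepts and baseline weeks are in the outcome, that variation and its between-woman counterpart are omitted, and the test is anti-conservative. The size is about 11–25% type I error at a store correlation of 0.95 with women not varying in change, and about 25–54% at 0.80, against a nominal 5%. These figures assume normal outcomes and weekly residual variance of 0.49 to 2.0. The document cannot say where purchasing lies in this range, so neither a single inflation figure nor a claim that the 5% level certainly fails is warranted. The ambiguity affects the primary test and should be settled before analysis.

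**What to change.** State one of two models for the primary test.

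1. Model the 3–6 month weeks only, with each woman's baseline purchasing as covariate, a random store intercept (women still nested within stores) and the group main effect as the test. Fit the 0–3 month period separately, since putting both post periods into one random-intercept model let type I error reach 12%.
2. Keep the long format and the interaction, drop the redundant baseline covariate, and add random store-by-period and woman-by-period effects.

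Under either, base inference on the number of stores (32 − 2 = 30 degrees of freedom with 16 per arm). If the chosen count or binary model offers only z-tests, report a store-level t-test as a check.

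The cost is wording, code and slightly more analysis work. Intervals will be wider than a random-intercept interaction would give. The design allowed for this: at a store correlation of 0.80 the true SE of 0.053–0.067 is still below the 0.089 behind the planned power.

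### The primary purchasing model adjusts for a baseline that is also one of its outcome periods, so the named interaction is the unadjusted difference in changes

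*Protocol article*

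**What the plan says.** The Primary outcome section defines a change: "The primary outcome is change in participant’s weekly fruit and vegetable purchasing patterns from baseline (3 months prior to refurbishment) to the 3–6 months period".

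The Statistical analysis section plans "three-level multilevel models, with women’s weekly purchasing data clustered within women, who are clustered within stores". It then names the effect: "With the data in ‘long’ format, an interaction between intervention group and time period will indicate whether there is a difference in change in sales", with the change running "from the 3-month baseline period to the 0–3 months and 3–6 months periods postintervention between the control and intervention stores". The next sentence adds the baseline as a covariate in the same models: "These models will be adjusted for sales from the 3-month baseline period as an efficient analysis of the changes in purchasing", and gives as a further reason "taking account of regression to the mean".

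For women's diet quality the same section describes an ordinary baseline-adjusted regression of the follow-up score, with "intervention group as the exposure and baseline diet scores included in the model to account for regression to the mean" and no period interaction.

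The Sample size calculations section powers a difference between the groups during the 3–6 month period: 0.3 item per week, SD 0.7, intraclass correlation 0.1, 16 stores per arm, 30 women per store, 90% power.

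**The concern.** An interaction can measure change from the baseline period only if baseline is a level of the period factor, that is, if the baseline weeks are outcome rows. The same baseline purchasing is then also placed on the right-hand side. The article does not say that baseline rows are dropped, that the covariate has a separate slope in each period, or that the arms are constrained to a common baseline mean. Any of these would change what the model estimates.

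Two different analyses are thus merged: a difference in changes and a baseline-adjusted comparison. In a randomised trial both would estimate the same effect. Here allocation follows a refurbishment programme and the stores are matched rather than randomised, so the two can give different answers. If the text does not settle which is primary, the choice can be made after the results are known.

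**Working it through.** **1. The plan's own figure.** Design effect 1 + (30 − 1) × 0.1 = 3.9. Effective number per arm 16 × 30 / 3.9 = 123.1. Standard error 0.7 × √(2/123.1) = 0.0892, and 0.3/0.0892 = 3.36. Power is 92.0% by the normal approximation and 90.2% by the noncentral t with 30 degrees of freedom. The stated 90% reproduces. It uses no baseline correlation, so nothing below changes it.

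**2. Algebra of the model as written.** For woman i in arm g and period p, let the mean be a + γg + τ_p + δ_p·g + βb_i, where b_i is her baseline purchasing. Least squares reproduces each arm-by-period mean. With complete data the arm average of b is the same in every period, so β times that average drops out of any change within an arm. Hence

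δ(3–6) = [mean at 3–6 months − mean at baseline, intervention] − [the same, control],

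whatever the value of β. This is the raw difference in changes.

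**3. Numerical check.** Simulated data had 16 stores per arm, 30 women per store, total SD 0.7, true effect 0.3 and a baseline–follow-up correlation of 0.5. The correlation is an assumption, because the article gives none for purchasing.
- In 1,000 data sets the interaction with and without the covariate agreed to within 3e-15.
- In a fit with a random intercept per woman, the estimate (0.3537) and its standard error (0.0450) were both unchanged by the covariate.
- With 30% of post-period rows missing, single estimates moved by up to 0.05, but the means stayed together (0.294 against 0.297).
- A negative binomial log-link check, with fixed effects and assumed parameters, gave mean interactions of 0.094 without and 0.095 with log baseline. The baseline-adjusted analysis gave 0.168.

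**4. Size of the disagreement.** Let d be the baseline gap between arms, f the gap at 3–6 months and β the within-arm slope of follow-up on baseline. The interaction is f − d and the baseline-adjusted effect is f − βd, so they differ by (1 − β)d. With d = 0.2 (assumed) and β = 0.5 (equal variances, correlation 0.5), the difference is 0.5 × 0.2 = 0.10 item, and 0.10/0.3 is one third of the target. With a true effect of 0.3:

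| Assumed course of the gap | f | Interaction, f − 0.2 | Baseline-adjusted, f − 0.1 | Simulated means |
|---|---|---|---|---|
| Persists in full | 0.5 | 0.3 | 0.4 | 0.297 and 0.402 |
| Shrinks to half | 0.4 | 0.2 | 0.3 | not simulated |
| Vanishes | 0.3 | 0.1 | 0.2 | 0.099 and 0.198 |

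The interaction is right in the first row and the baseline-adjusted effect in the second. In the third both fall short, the interaction by twice as much. With no baseline gap both averaged 0.30.

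**The case against.** The strongest reply is that the interaction is what the Primary outcome section asks for, a difference in change, and that only the explanatory clause about efficiency and regression to the mean is wrong. A term letting the baseline slope differ by period would make the 3–6 month interaction equal the baseline-adjusted effect (to within 3e-15 in simulation), and such a term is ordinarily left to an analysis plan. Much of this stands: the interaction is a valid estimator, and a coherent model is one unstated detail away. It does not remove the point. The article does not merely omit detail. It names an effect and attributes to it a property that the model as described does not give, and the missing detail decides which of two different estimates is primary.

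Three stronger readings are tempting and are not supported.

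- *The baseline-adjusted model must be primary.* With a gap that persists and no true effect, the interaction averaged −0.004 and the baseline-adjusted model 0.097, a false effect of about a third of the target. Persistent differences between non-randomised stores are plausible.
- *The plan loses power.* For unclustered individuals, the variance of the change analysis relative to the baseline-adjusted one is 2/(1 + r), or 1.33 at r = 0.5. The clustered simulations showed no such loss: empirical SDs were about 0.045 to 0.050 for the difference in changes and 0.049 to 0.059 for the baseline-adjusted analysis. Those runs held store effects constant over time and fitted no store term in the baseline-adjusted model, so they do not settle efficiency either way. The article also does not say whether 0.7 is the SD of a level or of a change.
- *The named test cannot detect the intervention effect.* If baseline rows were dropped and 0–3 months became the reference, the interaction would only compare the two post periods, and it averaged 0.00 under a constant effect of 0.3. That coding contradicts the article's statement that change is measured from baseline, and the group term of the same model recovered 0.299.

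**Conclusion.** The point holds as an error in how the primary model is specified. As written, the named interaction is the unadjusted difference in changes, and the claimed efficiency and control of regression to the mean do not apply to it. This is exact for a linear model with complete data and one common baseline slope. It was close to exact in a single negative binomial check with assumed parameters, which matters because the article has not yet fixed the distribution.

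The practical size, about 0.1 item, rests on an assumed 0.2-item gap and an assumed correlation of 0.5. It scales as (1 − β)d and is zero if the arms are balanced at baseline. The sample size calculation is unaffected. The other sections do not settle the choice: the outcome definition points to change, while the power calculation points to a group difference during 3–6 months.

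**What to change.** Before data are seen, replace the paragraph with one of two coherent models.

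(a) Keep the baseline weeks as outcome rows, remove the baseline covariate and the sentence on efficiency and regression to the mean, and name the group-by-period interaction for 3–6 months against baseline as primary. This fits the outcome defined as a change.

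(b) Use post-refurbishment weeks only as outcome rows with each woman's baseline mean as covariate (or keep the baseline rows and add a baseline-by-period term), and name the group effect at 3–6 months as primary. This delivers the property now claimed and fits the contrast that was powered.

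Pre-specify the other as the sensitivity analysis, because without randomisation the two rest on different assumptions about baseline gaps. State briefly why the chosen one is primary. The cost is the rewording of one paragraph, with no new data and no change to the sample size.

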### Secondary objectives

To assess effect modification by educational attainment on women’s change in fruit and vegetable purchasing.To assess how the intervention affects women’s dietary quality and daily fruit and vegetable intake, and the dietary quality of their young children.To assess how the intervention influences weekly store sales of fruit and vegetables.To conduct an economic evaluation from individual, retailer and societal perspectives.To conduct a detailed process evaluation to examine: (1) intervention implementation in each store and the exposure and reach to participants, (2) mechanisms of intervention impact by exploring the experiences of participants and staff, and (3) how contextual factors, such as social influences, spatial access to supermarkets and government policy, influence intervention effects.

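### The education test uses group × education with no time period, so it does not isolate modification of the change in purchasing at 3–6 months

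*Protocol article*

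**What the plan says.** The first item under Secondary objectives is "To assess effect modification by educational attainment on women’s change in fruit and vegetable purchasing". The quantity whose modification is sought is therefore a change.

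The Primary outcome section defines that change: "The primary outcome is change in participant’s weekly fruit and vegetable purchasing patterns from baseline (3 months prior to refurbishment) to the 3–6 months period" after refurbishment.

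The Statistical analysis section describes the purchasing models in two sentences that matter here. The first names the term for the intervention effect: "With the data in ‘long’ format, an interaction between intervention group and time period will indicate whether there is a difference in change in sales". The rest of that sentence sets baseline against each of the two follow-up windows and compares the arms on that basis. The second adds a covariate: "These models will be adjusted for sales from the 3-month baseline period as an efficient analysis of the changes in purchasing".

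For education, the same section proposes "including a multiplicative interaction between intervention group and education level in the individual purchasing models" and continues: "If there is evidence of an interaction, stratified analyses will be performed". No time period is attached to the education interaction.

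**The concern.** In a model where the intervention effect is group × period, modification of that effect by education is group × period × education. A group × education term answers a different question: whether the arm contrast differs by education when all rows in the model are pooled. If baseline rows are among them, a third of the pooled contrast comes from weeks in which no intervention effect can exist.

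Two errors could follow. Real modification is diluted. A pre-existing difference between arms in the education gap also enters the estimate, and because stores are not randomised (Study setting) such a difference cannot be ruled out. The test also acts as a gate for the stratified analyses, so an error in it determines whether education-specific effects are examined at all. The Introduction singles out differential effects by socioeconomic status as especially important to policy-makers.

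**Working it through.** **Figures in the plan.** No power or effect size is stated for the education interaction, so there is no figure to reproduce on this point. The primary power statement is not in dispute. With 16 stores per arm, 30 women per store and ICC 0.1, the design effect is 1 + 29 × 0.1 = 3.9 and the effective size is 480/3.9 = 123.1 per arm. A difference of 0.3 with SD 0.7 then gives 92.0% (normal) or 90.2% (t, 30 df), against the stated 90%.

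**Set-up.** There are three periods of equal length (baseline, 0–3 and 3–6 months, from Statistical analysis). Let *b* be the difference between two education levels in the arm contrast at baseline, and *m1* and *m2* the true modification of the change at 0–3 and 3–6 months. The education difference in the arm contrast is then:

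- baseline: *b*
- 0–3 months: *b* + *m1*
- 3–6 months: *b* + *m2*

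The target set by the objective and the primary outcome is *m2*.

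**What each model estimates** (linear outcome; ρ is the within-woman correlation between baseline and follow-up):

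- Two-way term, baseline rows included, no baseline covariate: *b* + (*m1* + *m2*)/3.
- Two-way term, baseline rows included, with the planned covariate: the pooled slope on baseline is (1 + 2ρ)/3, which leaves (*m1* + *m2*)/3 + 2*b*(1 − ρ)/3.
- Two-way term, follow-up rows only, baseline as covariate: (*m1* + *m2*)/2 + *b*(1 − ρ).
- Three-way term, 3–6 months versus baseline: (*b* + *m2*) − *b* = *m2*.

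**Assumed values, not in the documents:** woman-level SD 0.5 and residual SD 0.5, so ρ = 0.25/(0.25 + 0.25) = 0.5; half the women in each education level; modification 0.30; the baseline gaps shown below.

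| Scenario | Two-way, baseline rows + covariate | Two-way, follow-up rows only | Three-way, 3–6 months |
|---|---|---|---|
| *m1* = *m2* = 0.30, *b* = 0 | 0.20 | 0.30 | 0.30 |
| *m1* = 0, *m2* = 0.30, *b* = 0 | 0.10 | 0.15 | 0.30 |
| no modification, *b* = 0.20 | 0.07 | 0.10 | 0.00 |
| no modification, *b* = 0.30 | 0.10 | 0.15 | 0.00 |
| *m1* = *m2* = 0.30, *b* = −0.20 | 0.13 | 0.20 | 0.30 |

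Least-squares fits to simulated data agree. With 400,000 women, rows 1, 2, 4 and 5 gave 0.199, 0.099, 0.100 and 0.134 for the first model; 0.298, 0.148, 0.150 and 0.201 for the second; and 0.303, 0.304, 0.005 and 0.304 for the third. In a separate simulation of 40,000 women, row 3 gave 0.071 for the two-way term with the covariate and −0.003 for the three-way term.

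The fractions in the first two rows (two thirds and one third) follow from the three equal periods and do not depend on ρ. The leakage in rows 3 to 5 does depend on ρ.

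**The case against.** The strongest defence has four parts.

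1. The article is condensed, does not say that the interaction is two-way only, and states its aim as effect modification. A statistician fitting the purchasing models could take that to mean education modifying the group × period effect. This stands in part, since the full plan may be clearer. But the article does name a term, and the term it names has no period. Followed as written, it does not test what the objective asks, so this is more than missing detail.

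2. Adjustment for baseline sales is the language of analysis of covariance. With follow-up rows only, group × education is a legitimate test. This stands as an alternative reading, but it conflicts with the sentence saying that group × period shows the change from baseline. It also averages the two follow-up periods, so it does not target 3–6 months.

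3. A follow-up-only model also lets a baseline gap through: 0.15 for a gap of 0.30, against 0.10 for the long-format two-way term with its covariate. This stands. Leakage alone does not separate the written text from a follow-up-only analysis; dilution over periods is the firmer part of the concern.

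4. Stratified purchasing models would still give education-specific group × period effects. This also stands. The exposure is in the test and the decision that it governs.

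A reader might go further and infer that a baseline gap passes through in full (0.20 for a gap of 0.20), or that a true 0.30 could vanish when the gap is −0.20. Both figures require dropping the baseline covariate, which the plan says is included; with it they are 0.07 and 0.13. A reader might also call the interaction test underpowered. The article claims no power for it and no calculation has been made here, so that is not asserted.

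**Conclusion.** The concern holds as a wrongly specified test for the first secondary objective, and it is a should-fix. If baseline weeks are outcome rows, the named coefficient recovers about two thirds of a modification present in both follow-up periods and about one third of one confined to 3–6 months, and it picks up part of any baseline arm-by-education difference. If only follow-up rows are used, it is a valid form of test aimed at the average of two periods instead of the primary window. Under either reading the gate on stratified analyses can open or stay shut for the wrong reason.

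The sizes rest on a linear outcome, equal periods, no store clustering in the illustration, and assumed variances and gaps. The plan envisages a negative binomial or binary model, so the item-scale figures do not carry over directly to a log or odds scale; the pooling over periods does.

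The documents do not support the stronger conclusion that the inequality question is bound to be answered wrongly. The primary estimate and sample size are untouched, and the stratified models, if run, address the right effect.

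**What to change.** State in Statistical analysis that effect modification by education will be tested with group × period × education, including all lower-order terms, and that the decision rests on the contrast of 3–6 months with baseline.

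If the primary model is instead restated with follow-up rows only and baseline as a covariate, test group × education at 3–6 months and acknowledge that baseline adjustment removes a baseline gap only partly. Under the assumptions above, half of the gap remains.

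Preferably, also report the education-specific 3–6 month effects with 95% confidence intervals from that single model, whatever the interaction p value. Gating on an interaction test is a common convention, so this last part is a recommendation and not the correction of an error.

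The cost is about one sentence of analysis text, with no new data and no change to recruitment. It should be settled before outcome data are analysed, so that the choice of term is not made after the fact.
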